#### Survival analysis

PFS and OS will be estimated using the Kaplan–Meier method, and groups will be compared with the log-rank test. The Cox proportional hazards model will be used to estimate hazard ratios (HRs) and corresponding 95% confidence intervals, with potential adjustment for prespecified stratification factors. Proportional hazards assumptions will be checked using Schoenfeld residuals.

### Additional analyses

Interim analysis for safety and futility is planned after 50% of the planned PFS events have been observed. A futility boundary will be defined using the Lan-DeMets O’Brien-Fleming spending function. The DMC will have clear decision authority regarding continuation, modification, or termination.

Subgroup analyses are prespecified based on factors such as EGFR mutation subtype (e.g., exon 19 del vs. L858R), baseline TCM syndrome score severity, and presence of brain metastases. These analyses are explicitly labeled as exploratory due to limited power for interaction testing.

Logistic regression analysis will be employed to explore factors influencing tumor response rates. A two-sided *p* < 0.05 will be considered statistically significant for the primary endpoint. No adjustment for multiple comparisons will be made for exploratory secondary endpoints, and results for these will be interpreted as hypothesis-generating.

#### Safety population

All randomized participants who received at least one dose of study treatment.

### Trial status

Participant enrollment commenced in January 2026 and is scheduled to conclude by December 2026. As of the revision date (July 2026), 38 patients have been enrolled. The final follow-up for the primary endpoint assessment is projected by December 2027. Database lock and final data analysis are planned for Q1 2028. This study protocol (Version 1.0, April 2025) was finalized prior to the initiation of participant recruitment. No amendments have been made since protocol version 1.0.

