### Sample size

The sample size for this study was calculated based on the primary outcome of progression-free survival (PFS). Based on the FLAURA trial, the median PFS for osimertinib monotherapy is approximately 18.9 months. To achieve 80% power at a two-sided significance level of α = 0.05 for detecting a clinically meaningful difference, a target hazard ratio (HR) of 0.66 was assumed, corresponding to a median PFS of approximately 28.6 months in the experimental group (an absolute extension of 9.7 months). This effect size is consistent with the HR observed in the CATLA trial (HR 0.68).

Using the Schoenfeld formula for the log-rank test, the required number of PFS events (d) is calculated as:
$$d=4\times {\left(Z\_(1-\alpha /2)+Z\_(1-\beta )\right)}^{2}/{\left(\ln\;\mathrm{HR}\right)}^{2}$$

With α = 0.05 (two-sided), β = 0.20 (power = 0.80), Z_(1-α/2) = 1.96, Z_(1-β) = 0.84, and HR = 0.66:
$$d=4\times {\left(1.96+0.84\right)}^{2}/{\left(\ln\;0.66\right)}^{2}\approx 176\;\text{events}$$

Under a 1:1 randomization ratio with an accrual period of 12 months, a minimum follow-up of 12 months, and an expected event rate of approximately 65% at the end of follow-up, the required total sample size is approximately 270 patients (135 per group). Accounting for an estimated dropout rate of approximately 20%, we plan to enroll 200 patients (100 per group) to ensure that sufficient patients complete the primary endpoint assessment. The planned enrollment of 200 patients is expected to yield approximately 130 PFS events, providing approximately 75% power at the planned analysis. An interim analysis for futility is planned after 50% of the expected PFS events have been observed, with the option to increase sample size if warranted by conditional power calculations.

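### With 38 of 200 patients enrolled by July 2026, the unchanged December 2026, December 2027 and Q1 2028 dates need a 4- to 6-fold faster accrual rate, so the stated size, dates and event count are very unlikely to be met together

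*Protocol article*

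**What the plan says.** The Trial status section of the protocol article sets the calendar: "Participant enrollment commenced in January 2026 and is scheduled to conclude by December 2026". It then gives the count, "As of the revision date (July 2026), 38 patients have been enrolled", and goes on: "The final follow-up for the primary endpoint assessment is projected by December 2027" and "Database lock and final data analysis are planned for Q1 2028". It adds: "No amendments have been made since protocol version 1.0".

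The Sample size section builds the design on "an accrual period of 12 months, a minimum follow-up of 12 months, and an expected event rate of approximately 65% at the end of follow-up". It plans 200 patients, 100 per group, and expects about 130 PFS events and about 75% power. The Trial design section specifies a single centre. The only adaptation offered is a possible increase in sample size at the interim analysis, which is set at half of the expected PFS events.

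**The concern.** The enrolment count stands beside dates that take no account of it. Accrual time and follow-up time are inputs to the expected number of events, and the article ties the final analysis to a calendar date rather than to an event count. A shortfall in accrual therefore becomes a shortfall in events.

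There are two ways this can go at the reported pace. If the dates are kept, PFS is compared in about a third of the planned patients, with power so low that a null result would say little. If 200 patients are kept, the lock date falls before the last patient is randomized, and the 12-month minimum follow-up cannot be met by December 2027. The interim sample-size option would only widen the gap.

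**Working it through.** **Inputs.** From Trial status: start January 2026, enrolment end December 2026 (month 12), 38 enrolled by July 2026, final PFS follow-up December 2027 (month 24), lock in Q1 2028 (months 24–27). From Sample size: 200 patients, 12 months' accrual, 12 months' minimum follow-up, medians 18.9 and 28.6 months, HR 0.66, two-sided α = 0.05, about 20% dropout. The day in July is not given, so elapsed time is taken as 6 to 7 months.

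**The plan's own figures.** 200 × 0.65 = 130 events reproduces. Power for d events is Φ(|ln HR| × √d / 2 − 1.96). With d = 130 and |ln 0.66| = 0.4155 this is Φ(2.369 − 1.96) = Φ(0.409) = 66%, not 75%.

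**Accrual.**
- Share enrolled: 38/200 = 19%, after 6/12 to 7/12 = 50–58% of the window. Even accrual would have given 100–117.
- Observed rate: 38/7 = 5.4 to 38/6 = 6.3 per month.
- Needed for the remaining 162: 162/6 = 27 to 162/5 = 32.4 per month. The ratios are 27/6.33 = 4.3 and 32.4/5.43 = 6.0.
- Enrolled by December 2026 at the observed rate: 12 × 5.43 = 65 to 12 × 6.33 = 76.
- Time to 200: 200/6.33 = 31.6 to 200/5.43 = 36.8 months, about August 2028 to January 2029.

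**Events without dropout.** With uniform accrual over A months and analysis at month T, the event probability per arm is 1 − [e^(−λ(T−A)) − e^(−λT)] / (λA), where λ = ln 2 / median. This gives λ = 0.0367 (control) and 0.0242 (experimental).

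| Scenario | A, T (months) | Control | Experimental | Mean | Patients | Events | Power |
|---|---|---|---|---|---|---|---|
| Close in December 2026 at observed pace | 12, 24 | 0.479 | 0.351 | 0.415 | 65–76 | 27–32 | 19–21% |
| All 200 at 6.3 per month, plus 12 months | 31.6, 43.6 | 0.619 | 0.478 | 0.548 | 200 | 110 | 59% |
| All 200 at 5.4 per month, plus 12 months | 36.8, 48.8 | 0.647 | 0.506 | 0.576 | 200 | 115 | 61% |

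The last two rows end in about August 2029 and January 2030. At the observed pace, 130 events arrive at about month 52–55.

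**Events with dropout.** The article does not say over what period its 20% applies. I assume exponential censoring at a constant rate η, reaching 20% by 24 months (η = 0.0093) or by 12 months (η = 0.0186).
- Closing in December 2026: about 25–29 events (20% by 24 months) or 23–27 (20% by 12 months).
- All 200 plus 12 months: about 98–102 or 88–91 events, which is about 50–56% power.
- Reaching 130 events: about month 67–70 with 20% by 24 months. With 20% by 12 months it is never reached, because the ceiling is 200 × the mean of λ/(λ + η) = 200 × (0.663 + 0.566)/2 = about 123.

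**Interim.** Half of 130 is 65 events. Closing in December 2026 at the observed pace gives 27–32 events by December 2027, so the interim would not be reached.

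**The case against.** A reader might infer that the calendar cannot deliver 200 patients and that the article contradicts itself. The documents do not support that. They give one cumulative count at one date, with no monthly figures. A straight line through the first 6–7 months ignores any start-up lag, and the later dates are worded as forecasts. Acceleration is possible, and the article condenses a full protocol that may hold a recruitment contingency. What remains is that the required acceleration is 4- to 6-fold at one centre. The text was revised once the count was known, and it neither acknowledges the shortfall nor moves a date.

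A reader might also infer that the trial will be analysed on 65–76 patients with about one-fifth power. That is what the dates deliver at the observed pace if they are kept. It is not a stated intention, because 200 remains the target throughout, and late completion may be the likelier outcome. Slow accrual by itself does not bias the estimate or inflate type I error.

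It can be said that this is trial conduct rather than a planning error. In part it is: the 12-month accrual was a design assumption made before recruitment began. But the expected events and power rest on it and are still presented as current.

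Finally, the 65% event rate and the 75% power do not reproduce even with accrual on schedule. Those are separate problems. Correcting them would leave these dates unchanged, and this point does not depend on them.

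**Conclusion.** The concern holds as one of feasibility and of consistency between the stated size, dates and event count. Meeting the published calendar with 200 patients is very unlikely at the reported pace. Keeping the dates would leave at most about 21% power. Keeping 200 patients moves the end of enrolment past the lock date and, with the minimum follow-up added, the analysis to about August 2029 to January 2030, with fewer than the stated 130 events.

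The accrual figures assume enrolment from the beginning of January 2026 and a constant rate. The event figures also assume exponential PFS at the plan's medians, and the higher figures ignore dropout. The direction does not depend on the dropout assumption, since dropout only lowers the counts.

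**What to change.** 1. In Sample size and Trial status, replace the 12-month accrual period and the December 2026, December 2027 and Q1 2028 dates with a projection from actual accrual, shown as a range. On the single reported count, that is about 32–37 months to enrol 200. The sponsor's monthly figures should refine it. Any measure expected to raise accrual should be stated, with its assumed effect.
2. State that the primary analysis takes place when a named number of PFS events has occurred and the last patient has had the 12-month minimum follow-up. One option is the plan's 130 events: about month 52–55 without dropout, later or possibly unreachable with it, and 66% power two-sided. The other is a lower count with its power restated, for example 110 events with about 59%.
3. State the dropout assumption, with its period, that the projection uses.
4. If December 2027 must stay, restate the patients, events and power that date delivers, and say whether the interim analysis can still occur.

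The cost is an amendment through the ethics committee route that the Ethics and dissemination section already describes, together with less favourable published dates or power. No patients beyond the planned 200 are needed. If 200 is kept, the trial runs longer, which the observed pace already implies.

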### Ethics and dissemination

This trial will be conducted in full conformity with the ethical principles outlined in the Declaration of Helsinki. The study design also adheres to the Standard Protocol Items: Recommendations for Interventional Trials (SPIRIT) 2025 Statement (20) and the SPIRIT-TCM Extension 2018 (21) for traditional Chinese medicine trials. The study protocol and informed consent forms have been reviewed and approved by the Medical Ethics Committee of Shuguang Hospital, affiliated with Shanghai University of Traditional Chinese Medicine (Approval No.: 2025–1739–079-02). Any subsequent amendments to the protocol will require submission and approval by the same ethics committee before implementation. Written informed consent will be obtained from each participant prior to any study-specific procedures. The trial is registered with the International Traditional Medicine Clinical Trial Registry (ITMCTR2025002306). Upon completion of the study, the results will be submitted for publication in peer-reviewed international scientific journals, regardless of the outcome. Findings will also be presented at relevant scientific conferences. Authorship eligibility will be determined based on the International Committee of Medical Journal Editors (ICMJE) criteria, reflecting substantial contributions to the work. Data sharing will be considered following publication, in accordance with applicable data protection regulations and participant consent.

## Discussion

Acquired resistance to EGFR-TKIs remains a major challenge in the management of advanced EGFR-mutant NSCLC, often developing within the first year of therapy. Although third-generation osimertinib has extended median PFS to approximately 18.9 months, resistance eventually develops in nearly all patients (22). Early adjunctive interventions that may modulate the internal environment and support patient resilience could provide an opportunity to delay the onset of resistance. This trial is designed to evaluate whether adding Yifeixiaoji Decoction (YFXJD) to standard osimertinib therapy can influence clinical outcomes when administered before resistance emerges.

YFXJD is a multi-herb TCM formula developed based on the principles of “supplementing qi, nourishing yin, detoxifying, and resolving masses.” Preclinical studies suggest that components of the formula, particularly Dioscorea nipponica and *Punica granatum* pericarp, may affect immune function, inflammatory responses, and tumor cell behavior *in vivo*, and preliminary clinical observations indicate potential benefits in symptom management and quality of life. These findings provide a rationale for investigating YFXJD in combination with osimertinib therapy, without presuming that it can reverse established resistance.

This study employs a randomized, double-blind, placebo-controlled design with two parallel groups, ensuring rigorous evaluation of YFXJD in a controlled setting. Key methodological strengths include: (1) the use of a single contemporary EGFR-TKI (osimertinib) to eliminate treatment heterogeneity; (2) blinded independent central review of radiographic endpoints; (3) a comprehensive biomarker panel to explore potential mechanisms; and (4) adherence to SPIRIT 2025 and SPIRIT-TCM 2018 reporting standards.

In addition to clinical endpoints, the trial incorporates exploratory biomarker assessments, including immune and inflammatory parameters, to provide mechanistic insights. These features strengthen the ability to generate reliable data regarding the safety and potential efficacy of the integrative approach.

Several limitations should be considered. As a single-center trial, the findings may have limited generalizability due to local clinical practices and participant characteristics. The complex composition of YFXJD and the limited scope of biomarker analysis constrain mechanistic understanding. Standardizing TCM syndrome differentiation within a clinical trial framework remains challenging. Fourth, the exploratory biomarker analyses are hypothesis-generating and require validation in future studies. Finally, although the use of osimertinib as a uniform background therapy addresses the heterogeneity concern raised by prior studies, the sample size may still be insufficient for robust subgroup analyses.

The CATLA trial (6) previously demonstrated that adding an unspecified Chinese herbal formula to first-generation EGFR-TKIs prolonged PFS. The ongoing CATLA-2 trial (7) is evaluating YYJD combined with osimertinib. Our trial complements these efforts by evaluating a distinct formula (YFXJD) with a different composition and preclinical rationale in a uniform osimertinib background. Positive results would provide evidence for a specific TCM formula that could be integrated into standard osimertinib therapy, while negative results would help refine the selection of herbal formulas for future investigation.

Future multi-center studies with larger sample sizes and more comprehensive mechanistic analyses—including serial ctDNA monitoring and paired tissue analysis at progression—will be necessary to confirm and extend these findings and to establish whether YFXJD specifically affects molecular resistance mechanisms.
